#### 9.2.7 Pin-prick pain threshold (BI-participants)

Pin-prick pain thresholds (PPTs) in the primary BI-area and in the secondary hyperalgesia area are assessed by “weighted-pin” stimulators (8 to 512 mN [81 to 10,424 kPa]), starting with the lightest pin-prick stimulator (8 mN), and applying a modified Dixon’s up-and-down technique. Participants are instructed to report the number of stimuli perceived as unpleasant after a total of five pin-prick stimuli. The lowest pinprick force associated with  $\geq 3$  unpleasant stimuli is defined as the PPT. The median value of the five PPTs is used in further data analysis. The PPT-data (8, 16, 32, 64, 128, 256, 512 mN) are converted to corresponding ordinal values 1 to 8, where the “cut-off” value of 8 is registered if no pain is elicited during assessment with the heaviest pin-prick stimulator (512 mN).

## 10. STUDY DRUG AND PHARMACY PROCEDURE

### 10.1 Study drug (all participants [except for 10.1.2 only for TME-participants])

#### 10.1.1 Naloxone

Naloxone 4 mg/ml is delivered in glass ampoules of 100 ml (total content 400 mg). Naloxone is dissolved in a 0.9% NaCl solution: 1 liter of solution contains 9 grams of sodium chloride in sterile water (sodium-chloride 154 mmol/l; osmolarity 308 mmol/l). The solutions are identical in regard to color, density, transparency and odor.

#### 10.1.2 Placebo

Placebo is normal saline delivered in glass ampoules of 100 ml. One liter of placebo solution contains 9 g of sodium chloride in sterile water (sodium-chloride 154 mmol/l; osmolarity 308 mmol/l).

#### 10.1.3 Rescue drugs

As rescue-analgesic the rapid-onset, opioid alfentanil, will be administered, which in less than one min completely will antagonize the effects of naloxone. Alfentanil is a well-known drug used in anesthesia for immediate relief of acute pain. Alfentanil is initially given 7-15 mikrog/kg (1-2 ml/70 kg) and is administered in a titrated fashion until the desired analgesic effect is achieved.

Other drugs that the investigator considers necessary for the management of adverse effects (adrenaline, atropine, midazolam, ondansetron) will be administered. The administration of rescue drugs will be recorded in the participant’s Case Report Form.

## **10.2 Blinding procedure, packing and labeling**

### **10.2.1 TME-participants and BI-participants**

This is a cross-over, block-randomized, double-blind study. Randomization (computer generated using Randomization.com; sequence-randomization in blocks of four subjects), and, manufacturing, packaging and labelling of drugs will be performed by Skanderborg Hospital Pharmacy (att. Pharmacist [name]). Two sets of non-transparent sealed envelopes with the complete randomization list will be prepared. These contain information on which treatment each participant participating in the study will receive. The sponsor stores one of the envelopes, while the other one is kept by the investigator at the Department of Anesthesiology HOC, 4231 Rigshospitalet in a secure locked place. The Skanderborg Hospital Pharmacy keeps the un-blinded randomization list, which will be sent to the investigator for data analysis after the study is finished. Individual drug-packages, for each participant, containing two 100 ml ampoules of normal saline and naloxone 4 mg/ml, respectively, include a sealed, non-transparent envelope containing the randomization sequence code, to be broken in case of a medical emergency (paragraph 12.4, page 29).

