## 3. OUTCOMES

### 3.1 Primary Outcome

#### 3.1.1 Impacted mandibular third molar extraction (TME) study

- A composite measure of pain (numerical rating scale [NRS]; 0 = no pain; 10 = worst perceivable pain) during rest + masticatory pain + pain during external algometry (100 kPa) at the injury site, assessed 4 weeks ( $\pm$  3 days) after uncomplicated extraction of an impacted mandibular third molar.

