## 9. METHODS

### 9.1 Study algorithms

#### 9.1.1 TME-study

[figure not shown]

**Fig 1.** Study layout for impacted third molar extraction (TME) participants. The general timelines of the impacted third molar extraction (TME) study. Information day (green bar) where participants are informed about the study. The day of surgery (red), the follow-up phone call (yellow; 2 weeks  $\pm$  3 days] after TME), the first examination day (Day 1; dark blue; 4 weeks  $\pm$  3 days]) and the second examination day (Day 2; blue; exactly 7 days after Day 1).

[figure not shown]

**Fig 2.** Test-algorithm Day 1/2 for TME-participants and Day 2/4 for BI-participants with superimposed naloxone plasma-concentration curves. Median plasma-concentration (red) with 95% CI (dashed black lines) during a three-step target-controlled-infusion (TCI). Naloxone is given at step one with 0.25 mg/kg, step two 0.75 mg/kg and step three 2.25 mg/kg. Yellow timeline columns represent ratings with Clinical Opiate Withdrawal Scale (COWS) and blue columns indicate sensory testing (pain during rest, movement and 100 kPa pressure; pressure algometry; secondary hyperalgesia area). **BL** = baseline assessments (-20" to -8"; please, observe for BI-participants baseline assessments are made - 2hrs 20"

to – 2hrs 8" before start of TCI); **S1** = step one assessments (15" to 25"); **S2** = step two assessments (39" to 49"); **S3** = step three assessments (65" to 75").

At the follow-up phone call 2 weeks ( $\pm$  3 days) after surgery any questions the participant may have regarding the study will be discussed. The post-surgical pain intensity and signs of post-surgical complications will be penetrated (swelling, pain, fever, malaise, excessive lymph-node swelling).

The study drug (naloxone or placebo) will be given in a randomized fashion on the examination days, Day 1 and Day 2. Day 1 takes place 4 weeks ( $\pm$  3 days) after surgery. Day 1 and Day 2, separated by exactly 7 days, are at Department of Neuroanaesthesia 3042, Rigshospitalet (Fig. 1). Procedures on Day 1 and Day 2 will be performed by a physician and a research-nurse.

The agenda for the examination days are:

#### 9.1.2.1.1 Day 1/Day 2

- Assessment of inclusion and exclusion criteria
- The participant gives his informed consent (only Day 1)
- The participant fills out the Hospital Anxiety and Depression Scale (HADS; only Day 1)
- The participant fills out the Pain Catastrophizing Scale (PCS; only Day 1)

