##### 9.1.2.1 Screening day: Day 0 (Fig. 3).

- The participants have been instructed to use a hair trimmer in the test areas on both lower legs, two days before each study session.
- Assessment of inclusion and exclusion criteria
- The participant gives his informed consent
- The participant fills out the Hospital Anxiety and Depression Scale (HADS)
- The participant fills out the Pain Catastrophizing Scale (PCS)

- The examiner fills out the Clinical Opiate Withdrawal Scale (COWS)
- Brief medical examination:
  - Medical history
  - Auscultation of heart and lungs
  - Blood pressure and heart rate
  - Routine palpation of lymphatic nodes in the submandibular regions, the supraclavicular fossae and the axillae.
  - Assessment of deep tendon reflexes
- Urine-sample to test for opioids (sample is discarded just after the analysis).
- **Baseline assessments** (all sensory assessments are made at the **left** leg):
  - The corners of the BI-area is outlined by a marker on the medial aspect of the lower leg with the upper margin 11 cm below the medial meniscus and the anterior border 7 cm behind the anterior margin of the tibia.
  - The secondary hyperalgesia area is determined using a “weighted-pin” stimulator (cf. 9.2.5.2). A **green** marker is used to indicate the transition zone.
  - Pin-prick pain thresholds (PPTs) in the primary BI-area and in the secondary hyperalgesia area are assessed by “weighted-pin” stimulators (cf. 9.2.7) .
- **Burn injury induction:**
  - A first-degree BI is induced by a computerized contact thermode (MSA Thermal Stimulator, Somedic AB, Hörby, Sweden; 5.0 x 2.5 cm^2; 47.0°C, 420 s) applied with gentle pressure at the pre-specified area.
  - Pain intensity is assessed by NRS (0-10) during the BI-induction (cf. 9.2.4.2).
- **Post-injury assessments:**
  - **Time 1 hr 7"** after start of induction, secondary hyperalgesia areas are demarcated (cf. 9.2.5.2), using a **red** marker.
  - PPT's are assessed, as described above.
  - The demarcations of hyperalgesia areas are transferred to clear acetate sheets.
  - The sheets are scanned, and calculations of the octagon areas (total area minus the area of thermode) are by a computer program (Canvas 12.0, ACD International Systems, Victoria, Canada).
  - The participants are allocated to low-sensitizers and high-sensitizers

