#### 9.1.2.2 Burn injury days: Day 1 (right leg)/Day 3 (left leg; [Figs. 3 and 4]):

- The participants have been instructed to use a hair trimmer in the test areas on both lower legs, two days before each study session.
- It is verified that the participant belongs to either the low-sensitizer group or the high-sensitizer group.
- Urine-sample to test for opioids (sample is discarded just after the analysis).
- **Baseline assessments**, as previously described (Day 0; Fig. 4).

- **Burn injury induction**, as previously described (Day 0; Fig. 4).
  - **Post-injury assessments**, as previously described (Day 0; Fig. 4). However, an additional 2 hrs post-injury assessment is made at **time 2 hrs 7"** after induction of the burn injury (cf. 9.2.5.2), using a **green** marker.

[figure not shown]

**Fig 3.** General study layout for the burn injury (BI) study. BIs are induced Day 0, Day 1 and Day 3. Day 0 is a screening day, including high-sensitizers (large secondary hyperalgesia areas; 75% quartile) and low-sensitizers (small secondary hyperalgesia areas 25% quartile). Day 1 and Day 3 include induction of BIs in high- and low-sensitizers. Target-controlled-infusion (TCI) days are Day 2 and Day 4, with randomized allocation between placebo and naloxone. The time line between Day 1 and Day 2, and, Day 3 and Day 4, is 7 days. The timeline between Day 3 and Day 0 is 8 weeks or more.

[figure not shown]

**Fig 4.** Study layout for the burn injury (BI) study. Day 1/Day 3 includes induction of BI (mild thermal injury; 47C°, 7") with baseline assessments (green rectangle), burn injury (red) and post-injury assessments (blue). Day 2/Day 4 include a pre-drug assessment (blue; post-injury 165 hrs), drug-infusions (naloxone or placebo; 167-168 hrs) and assessments during target-controlled-infusion ([TCI]; light green). The estimated plasma concentrations are superimposed in dashed red line. Roman numerals indicate the three TCI-steps. Stars indicate assessments of pin-prick pain thresholds (red), and secondary hyperalgesia areas (green star).

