#### 9.1.2.3 TCI-days: Day 2 (right leg)/Day 4 (left leg; [Figs. 3 and 4]):

The study drug, naloxone will be given by a TCI-regimen at the Multidisciplinary Pain Center 7612 or Department of Neuroanaesthesia 3042, both at Rigshospitalet. Procedures on the study day will be performed by a physician and a research-nurse.

- The participants have been instructed to use a hair trimmer in the test areas on both lower legs, two days before each study session.

- The examiner fills out the Clinical Opiate Withdrawal Scale (COWS).
  - Urine-sample to test for opioids (sample is discarded just after the analysis).
  - Online Reaction Time is measured, as previously described (Day 0).
  - Randomization (consecutively by pre-specified randomization)
  - Monitoring with three-lead ECG and measurements of pulse oximetry, blood pressure and respiratory rate is started.
- 
- **Time 165 hrs** after induction of the BI Baseline, **Baseline assessments**, as previously described (Day 0), is performed (Fig. 4). A **blue** marker is used to demarcate the secondary hyperalgesia area.
  - **Time 167 hrs 20" to 167 hrs 45": First** step target-controlled-infusion (TCI; including a bolus dose) of naloxone/placebo infusion (Fig. 4).
  - **Time 167 hrs 33" to 167 hrs 35":** The examiner assesses COWS-rating.
  - **Time 167 hrs 35" to 167 hrs 45":** Identical assessments as made at baseline are repeated. A **red** marker is used to demarcate the secondary hyperalgesia area.
  - **Time 167 hrs 45" to 168 hrs 10": Second** step TCI (including a bolus dose) of naloxone/placebo infusion (Fig. 4).
  - **Time 167 hrs 57" to 59":** The examiner assesses COWS-rating.
  - **Time 167 hrs 59" to 168 hrs 09":** Identical assessments as made at baseline are repeated. A **green** marker is used to demarcate the secondary hyperalgesia area.
  - **Time 168 hrs 10" to 168 hrs 35": Third** step TCI (including a bolus dose) of naloxone/placebo infusion (Fig. 4).
  - **Time 168 hrs 23" to 168 hrs 25":** The examiner assesses COWS-rating.
  - **Time 168 hrs 25" to 168 hrs 35":** Identical assessments as made at baseline are repeated. A **black** marker is used to demarcate the secondary hyperalgesia area.
  - **Time 168 hrs 35":** End of naloxone/placebo infusion.
  - Monitoring data are continuously registered and documented.
  - Potential side-effects are continuously registered and documented

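### Period is tied to leg and earlier burn (BI) and to week after surgery (TME), yet no primary analysis contains it and no stratification of the BI list by sensitizer group is described

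*Protocol*

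**What the plan says.** **Allocation.** Protocol 10.2.1 covers both studies and describes "sequence-randomization in blocks of four subjects". Section 9.1.2.3 adds, for the BI infusion days, "Randomization (consecutively by pre-specified randomization". Neither names sensitizer group as a stratum.

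**BI periods.** The section headings fix the leg by period for everyone: "Burn injury days: Day 1 (right leg)/Day 3 (left leg" and "TCI-days: Day 2 (right leg)/Day 4 (left leg". At the Day 0 screening burn (9.1.2.1), "all sensory assessments are made at the left leg". The legend to Fig 3 puts at least 8 weeks between Day 0 and Day 3.

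**TME periods.** Day 1 is 4 weeks ± 3 days after surgery, and Day 2 is "exactly 7 days after Day 1" (9.1.1, Fig 1). Section 3.1.1 sets the primary outcome at 4 weeks ± 3 days "after uncomplicated extraction of an impacted mandibular third molar".

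**Analysis.** The TME part of 13.2 lists TCI step, drug, secondary hyperalgesia area, pressure pain threshold, HADS and PCS, together with repeated-measures ANOVA or Friedman and paired t or Wilcoxon tests. The BI part (also numbered 13.2.1) lists secondary hyperalgesia area (SHA), sensitizer group, TCI step, HADS and PCS. Period, sequence and leg appear in neither. Both models drop terms with P > 0.05. The TME outcome, SPID, subtracts the same-day baseline (13.1.1, item 3). The BI quantity, ΔSHA, is the difference of maximum areas during infusion, with no baseline subtracted.

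**The concern.** In a crossover, anything that differs between the two occasions adds to the naloxone-minus-placebo difference in one sequence and subtracts from it in the other. Here the occasions do differ. In BI, period coincides completely with leg and with an earlier burn at the test site, and period 2 also follows a first study burn and infusion. In TME it coincides with an extra week of recovery.

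Without a period term there are two consequences. If the sequences are unequally represented, part of the period difference shifts the treatment estimate. Even when they are equal, the period difference remains in the residual and widens it.

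The BI primary quantity is the most exposed. It compares two sensitizer groups, so what matters is sequence balance within each group, and the described list does not secure that. With one balanced list, an excess of one sequence among high-sensitizers is matched by the opposite excess among low-sensitizers, so the two shifts add. The factor lists are written into the protocol, so this is not a detail left open for a later plan.

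**Working it through.** **1. The plan's own TME figure.** Inputs (13.1.1, Table 2): ΔSPID = 5; SD = √17 = 4.12 (correlation 0.5); α = 0.01, taken as two-sided because that reproduces the stated number; power 0.90. Paired t-test: 5/4.12 = 1.21; noncentrality 1.21 × √14 = 4.54 on 13 df; power 0.913. At n = 13 it is 0.880. So 14 is reproduced, as are the stated 9 and 19 for SD 3 and SD 5.

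**2. How period enters.** Let τ be the treatment effect and δ the period 2 minus period 1 difference. The within-subject difference (naloxone minus placebo) is τ + δ for placebo-first and τ − δ for naloxone-first. Its mean is shifted by δ × (n placebo-first − n naloxone-first)/n.

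**3. BI imbalance.** Assumption: one list of 40 with 20 per sequence, and 20 subjects per sensitizer group. The number in a given sequence among high-sensitizers is hypergeometric (40, 20, 20), and the low group mirrors it. At 12:8 the high group shifts by (12 − 8)/20 × δ = 0.2δ and the low group by −0.2δ, so the contrast shifts by 0.4δ.

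| Split in a group | Probability of this or worse | Shift in high-minus-low contrast |
|---|---|---|
| 11:9 | 0.75 | at least 0.2δ |
| 12:8 | 0.34 | at least 0.4δ |
| 13:7 | 0.11 | at least 0.6δ |

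**4. BI error rates.** This is a simulation of a simple two-group comparison of within-subject differences at α = 0.01. δ is in units of the SD of that difference, and the group difference is 1.25 SD. Both are assumptions; the documents give no period effect.

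| δ (SD) | Type I error at 13:7 vs 7:13, no period term | Type I error averaged over lists, no period term | Average power, no period term | Average power, with period term |
|---|---|---|---|---|
| 0.25 | 0.015 | 0.010 | 0.86 | 0.87 |
| 0.5 | 0.026 | 0.011 | 0.79 | 0.88 |
| 1 | 0.040 | 0.010 | 0.52 | 0.87 |

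With no period effect, power without the term is about 0.89. With the term, type I error stays at about 0.010 for each split simulated. Stratification alone is not enough: at exactly 10:10 in both groups but without a period term, δ = 0.5 SD still lowers power to 0.81, because the residual is inflated.

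**5. TME.** At 7:7 the mean shift is zero, but the residual sum of squares (divided by 17) becomes noncentral chi-square on 13 df with noncentrality 14δ²/17. With a period term the standard error is unchanged and the df fall from 13 to 12.

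| Assumed δ in SPID (NRS units) | Power, no period term | Power, with period term |
|---|---|---|
| 0 | 0.913 | 0.905 |
| 1 | 0.90 | 0.905 |
| 2 | 0.85 | 0.905 |
| 3 | 0.75 | 0.905 |

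Fourteen consecutive subjects split 7:7, or 8:6 with probability 1/3 (both members of the half-filled last block in the same sequence). At 8:6 the shift is 2/14 = 0.14δ, and power with a period term is 0.898. An extreme case is 18 randomised as 10:8 with all four drop-outs from the smaller sequence: 10:4 gives 6/14 = 0.43δ.

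**6. TME window.** Section 3.1.1: 28 ± 3 days, that is days 25 to 31. Day 2 is 7 days after Day 1, that is days 32 to 38. The ranges do not overlap, so every Day 2 assessment lies outside the window as worded.

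**The case against.** Sequence is randomised, so period is balanced in expectation. A reader might infer that the BI contrast is biased, or that false positives exceed 0.01 overall. The documents do not support that. Averaged over possible lists, type I error is about 0.010; the shift exists only given the imbalance that happens to occur. This stands and limits the point to conditional shifts and lost power.

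In TME, SPID subtracts the same-day baseline, so healing that moves baseline and infusion values equally cancels. The δ above must therefore be a period difference in change from baseline. The protocol's own assumed placebo change is 11 − 7 = 4 units, so δ of 2 or 3 would be large, and at 1 unit the loss is under 2 points. This stands too. That 14 is not a multiple of four is of little consequence.

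In BI, at least 8 weeks separate the two left-leg burns, and 4.2.2.1 says signs subside in most cases within 24 to 48 hours. The pilot figures in 13.1.2 imply a contrast of (111.0 − 2.1) − (0.9 − 0.3) = 108.3 cm². If δ equalled the high-sensitizer placebo SD of 2.5 cm², the shift at 12:8 or 13:7 would be 1.0 or 1.5 cm², about 1%. This is fair, but it rests on three subjects per group, which the protocol itself calls extremely limited, and on a period effect no larger than placebo variation. Neither can be relied on.

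Finally, lack of stratification is read from silence; separate lists may be intended. That is so, and the 34% and 11% depend on it. The missing period term does not.

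A reader might also take half the naloxone infusions to be protocol deviations. Sections 7.1.1 and 9.1.1 attach the 4 weeks to Day 1, so this is a wording conflict to reconcile.

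**Conclusion.** The point holds in a limited form. Period is completely confounded with leg and earlier burn in BI and with week after surgery in TME, and the analyses fixed in 13.2 ignore it. The result is a shift conditional on realised imbalance, plus an inflated residual; it is neither a systematic bias nor an inflated average type I error.

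It matters mainly in BI, where the outcome has no same-day baseline correction and the contrast adds the imbalance of the two groups: a 34% chance of a shift of at least 0.4δ and 11% of at least 0.6δ, if one unstratified list of 40 is used. In TME, blocking and baseline subtraction keep it modest: power 0.90, 0.85 or 0.75 instead of 0.91 for assumed δ of 1, 2 or 3 NRS units at 7:7. The size of δ is unknown in both studies. The case for change rests on the low cost of protection, not on evidence that a period effect exists.

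**What to change.** 1. Include period as a fixed effect, or use the period-adjusted paired comparison, in both primary analyses. State that it is exempt from the P > 0.05 backward elimination; otherwise it can be removed again. Cost: one degree of freedom. In TME at 7:7 with no period effect, power goes from 0.913 to 0.905, under one percentage point.
2. Block the BI sequence list separately for high- and low-sensitizers, or state that this is already so. Five blocks of four in each group of 20 give 10:10, and the shift in the contrast is then zero if all complete. Cost: one extra list with separately numbered packs. This has to be done before randomisation.
3. Reconcile the 4 weeks ± 3 days in 3.1.1 with a Day 2 that falls 7 days after Day 1. Cost: wording only.

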### **10.2.2 Manufacturing, packaging and labelling**

Manufacturing, packaging and labelling of drugs will be performed by Skanderborg Hospital Pharmacy (att. Pharmacist [name]).

## **10.3 Drug storage and accounting (all participants)**

The investigators are responsible for safe storage of the study drug and are accountable that the drug is solely provided to participants of this study. The investigators will supervise the balancing and accounting of the study drugs. The investigator is responsible for explaining and document any loss of study drug, and, in particular if there is any discrepancy between the received quantity and returned quantity of drugs.

## **11. DRUG ADMINISTRATION**

### **11.1 Target-controlled-infusion (all participants)**

The target-controlled-infusion (TCI) algorithm (Fig. 2) was calculated by the software NONMEM (7.3 ICON Development Solutions, Manchester, U.K. [property of UCSF, U.S.]), using computer simulations based on a population-kinetic model with 2,000 simulated administrations distributed on 10 subjects (Table 1). Thus a total dose of 3.25 mg/kg of naloxone will be administered in a step-wise approach for 75 minutes as follows (Table 1): In the first minute (0-1 min) a bolus of 0.02 mg/kg will be given followed by an infusion of 0.23 mg/kg during 24 minutes (1-25 min). Afterwards (25-26 min) a bolus of 0.06 mg/kg will be administered followed by a 24-minute infusion of 0.69 mg/kg (min 26-50). Finally a bolus of 0.18 mg/kg (50-51 min) will be given followed by a 24-minute infusion of 2.07 mg/kg (51-75 min). With this administration algorithm estimated naloxone plasma concentrations (median [95% limits]) of 344 ng/ml [130;567], 1,059 ng/ml [400;1,752] and 3,196 ng/ml [1,205;5,276] at time intervals 15-25 min, 40-50 min and 65-75 min, respectively, are achieved (Fig. 2). For TME-participants an identical infusion-algorithm will be used for the placebo infusion. All outcomes for TME-participants will be assessed before infusion and 3 times during infusion at the above mentioned

time intervals. In BI-participants blood-samples for pharmacokinetic outcomes are obtained at specified time-points during and after the TCI (cf. 9.1.2).

|                   | time (min)   | dose (mg/kg) | dose/70 kg (mg) | volume/70 kg (ml) | ml/min/70 kg |
|-------------------|--------------|--------------|-----------------|-------------------|--------------|
| Bolus 1    | 0-1   | 0.02         | 1.40            | 0.35              | 0.35         |
| Infusion 1 | 1-25  | 0.23         | 16.10           | 4.03              | 0.17         |
| Bolus 2    | 25-26 | 0.06         | 4.20            | 1.05              | 1.05         |
| Infusion 2 | 26-50 | 0.69         | 48.30           | 12.08             | 0.50         |
| Bolus 3    | 50-51 | 0.18         | 12.60           | 3.15              | 3.15         |
| Infusion 3 | 51-75 | 2.07         | 144.90          | 36.23             | 1.51         |
| TOTAL      |              | 3.25         | 227.50          | 56.88             |              |

**Table 1.** Naloxone (4 mg/ml) i.v.-administration: timeline, dose/kg, dose/70 kg, volume/70 kg and infusion-rates/min/70 kg for the three step target-controlled-infusion. The total naloxone-dose administered is 227.5 mg per 70 kg BW. The total naloxone volume is 56.9 ml per 70 kg BW.

